# 1. Introduction

## 1.1 Background

The prevalence of type 2 diabetes mellitus (T2DM) is increasing worldwide, with the greatest increase occurring in low- and middle-income countries [1] . The prevalence of diabetes is the highest in the Middle East and North Africa, with approximately 10.9% of the adult population being diagnosed with T2DM [2]. The estimated number of deaths caused by diabetes and its complications reached 368,000 in 2013 in the Middle East and North Africa [3]. In particular, diabetic kidney disease (DKD) is the leading cause of end-stage kidney disease and substantially contributes to cardiovascular events [4].

New approaches of managing patients with diabetes, such as pharmacist-led medication therapy management (MTM) [5], the use of telemedicine technology through mobile applications [6], dietary and exercise interventions [7, 8], and intensive serum electrolyte panel monitoring [9] have been shown to be beneficial for monitoring and managing diabetes complications, including DKD progression. However, the impact of each intervention or a combination of such interventions has not been clearly elucidated.

Although there is evidence demonstrating the benefit of individual interventions for reducing the burden of chronic T2DM and DKD, the most effective multi-factorial intervention, particularly on UAE population, remains unclear. Such an intervention is likely to involve glycaemic control by promoting adherence to medication and lifestyle, such as diet and exercise and closely monitoring to blood electrolyte levels. These factors have a long-term effect on DKD progression and hard end points, such as cardiovascular events and all-cause mortality [10].

In this study, we will examine the effect of these interventions in a combined multifactorial approach called Pharmacy Intervention Protocol (MPIP), and we will use the Abu Dhabi Health Services Company (SEHA) mobile application, which enables the patient to have access to his medical record, medications, and to book future appointments. The impact and usefulness of the application will be examined in the new pharmacy intervention protocol. Other studies have investigated similar tools in the treatment of patients with complex diseases, who require more frequent visits to achieve tighter glycaemic control or face difficulties in accessing the healthcare system [11].

Moreover, we will include a diet intervention involving pre- and post-diet assessments as well as physical activity assessments from the validated revised Summary of Diabetes Self-Care Activities measure, wherein a healthy diet plan with exercise counseling will be provided by a specialist dietician with the goal of optimising electrolyte levels, which have been demonstrated to be important in diabetes clinical outcomes, chronic kidney disease therapy and prevent progression to DKD [12]. However, more studies are warranted to prove causality.

Furthermore, we will use a stepwise approach to correct electrolyte imbalance which includes sodium, potassium and magnesium based on laboratory results, with diet as well as medication therapy modification to treat the patient’s electrolyte abnormalities. This approach has been utilized successfully in another case study to treat a patient who previously required intravenous replacement therapy for 16 years to treat electrolyte abnormalities [13].

Therefore, this randomized control trial will aim to investigate the effect of a multi-factorial intervention approach, involving pharmacist-led medication therapy management (MTM) with medication adherence, diet and exercise counselling, and optimisation of serum electrolyte levels on patients’ clinical outcomes, as well as kidney function in UAE national population with type 2 diabetes mellitus in ambulatory clinic.

## 1.2 Statement of The Problem

Up to our knowledge, this is the only research that will examine a new dimensions of multifactorial intervention approach to the local population of UAE. Limited studies investigate a multiapproach of pharmacist-led interventions in one research location to evaluate long-term adherence to medication and provide long term monitoring of eGFR to ensure that the patients are not receiving contraindicated or inappropriately high dose of medication as their eGFR declines in the progression of diabetic kidney. In addition, this research will try to explore novel solutions adapted to UAE culture to enhance adherence to dietary and exercise for type 2 diabetic patients with the aid of specialised dietitian.

Moreover, limited studies were conducted recently to investigate the effectiveness of correcting electrolyte imbalances, including serum hyponatremia, hypokalaemia, and hypomagnesemia in the progression of DKD. Few studies showed that such intervention may improve patients’ symptoms during the recovery from acute renal failure [14]. The encouraging results of the mentioned investigation have, consequently, provoked the interest in optimizing serum sodium, potassium, and magnesium to delay the progression of chronic kidney disease. Authors from several studies suggested potential avenues of future research to include investigating the effect of treating hyponatremia, hypokalaemia, and hypomagnesemia on the progression of diabetic kidney disease.

## 1.3 Research Aim, Objectives, and Outcomes

The study explores the possible interventions to improve patients’ therapeutic outcomes by medication adherence, structured diet, and exercise education. The research will investigate the impact of multifactorial interventions by pharmacists and clinical dietitian and electrolyte levels optimisation by physicians on the clinical outcomes in Emirati patients with type 2 diabetes.

The primary outcomes are as follows: (1) to evaluate the impact of pharmacist-led MTM on medications adherence, using a new pharmacist intervention protocol (MPIP), (2) to assess the effect of structure diet and exercise counseling with a specialized dietitian on anthropometry readings and carbohydrate as well as daily energy intake levels compared to control group, and (3) to assess the effect of the multi-factorial interventions on diabetic outcomes, including glycated haemoglobin A1c (HbA1c) level, blood pressure, and lipid profile.

The secondary outcomes are: (1) compare the effect of MPIP on regimen-specific medication possession ratio (MPR), and clinical interventions between both groups, (2) evaluate type, duration, and mean metabolic equivalent of task (METs) of physical activity per week during the follow up period between both groups, and (3) analyse serum electrolyte levels, cardiovascular risk factors, and eGFR levels in both group at study exit.

## 1.4 Hypothesis and Significance of The Research

In this research, we hypothesise that adherence to medication and exercise, in type 2 diabetic patients, will lead to improvement in patients’ clinical outcomes. The interventions in this research will offer recommendations for healthcare providers to adopt reliable measurable factors to improve diabetic outcomes, which eventually will lessen the burden of diabetes, medication cost in UAE and improve patient satisfaction by reducing or delaying macrovascular complications from diabetes.

In this study medication adherence will be measured by a validated Arabic version of medication adherence questionnaire, which is new in our region and in UAE. The revised Summary of Diabetes Self-Care Activities measure (SDSCA) scale will be used to evaluate adherence to diet and exercise was validated numerically. Moreover, the effects of different serum electrolytes levels including serum sodium, potassium, and magnesium levels on kidney function during the diabetes course will be investigated in this research.

The expected outcomes of the research are summarized as follow:

- Improve medication adherence measured by fixed medication possession ratio (MPR) equation and a validated questionnaire with the new pharmacy intervention protocol in the intervention compared to the control group.
- Achieve better exercise and diet adherence with overall reduction in total carbohydrate and energy intake in the intervention compared to the control group.
- Increase the number of patients reaching the target HbA1c level of < 7% and blood pressure target of 130/80 after one year in the intervention compared to the control group.
- Improved serum electrolyte levels (including serum Na, K, and Mg) in the intervention compared to the control group.
- Reduction in cardiovascular risk factors (such as wight and BMI) and improvement in eGFR levels in the intervention compared to the control group, within the study observation period.

## 1.5 Literature Review

The clinical consequence of diabetic complications and DKD are causing the most cost burden on any healthcare system. For example, the Australian commonwealth government suggest that if current trends on diabetic complications continue, spending for instant on the treatment for diabetic kidney disease will increase to $9.2 billion over the next 30 years. [15].

Many studies have investigated the correlation between pharmacist-led interventions through medication counselling in improving clinical outcomes and medication adherence in patients with T2DM [16, 17]. Moreover, the use of technology and telemedicine in disease management has been proven to be beneﬁcial in patients with diabetes and other chronic disease, demonstrating notable reduction in mortality rates [18]. Besides, the use of mobile applications can save time and effort and enable patients to manage their health more effectively [19].

In addition, several meta-analyses concluded that using carbohydrate-restricted diets in patients with type 2 diabetes resulted in better glycaemic control than control diets, they also reported different degrees of HbA1c reduction and weight loss, justified by the various levels of carbohydrate restriction in each study, and highlighted that these results are often impacted by factors other than low-carbohydrate content alone [20-23]. Moreover, several studies investigating low-carbohydrate diet interventions combined increased physical activity, and the total reduction in calorie intake with improved outcomes [24, 25].

Although several disease management models are available and supported by many healthcare systems to manage chronic diseases, such as chronic care models, and disease or case management programs to reduce long-term complications, disease cost, and overall disease burden [26], health systems do not support structured diet and exercise programs to help patients to better control their diet as well as lifestyle and improve quality of life, and focus on a self-care management approach under the guidance of family physicians or endocrinologists rather than a team approach that includes dietitians, diabetic educators, and pharmacists as part of diabetes care delivery systems [27].

Moreover, malnutrition and electrolyte imbalance are common in patients with diabetes who have chronic kidney disease and occur in varying degrees depending on the level/degree of kidney function [28]. Regular assessment of nutritional status using different measurements, proper diet history and counselling have been recommended by several existing guidelines as no single assessment can accurately determine the presence of malnutrition [12, 29].

Electrolyte disorders, which also coexist in several medical conditions, including hypertension and congestive heart failure [30, 31], were previously observed by Shahid and Mahboob during DKD progression in patients with diabetes compared with non-diabetic or normotensive patients [32]. This study showed a significant increase in erythrocyte intracellular sodium levels and a significant decrease in erythrocyte intracellular potassium, serum sodium and serum magnesium levels in patients with diabetes mellitus and nephropathy compared with those in euglycemic patients. Additionally, the attenuation of electrolyte abnormalities in patients with diabetes can reverse hyperglycaemia-induced effects on cellular transport processes and decrease NaK-ATPase function, suggesting that serum electrolytes, such as potassium and magnesium, can be considered indicators of DKD progression and play an important role in its treatment [33].

For instance, hypomagnesaemia may impair glucose excretion and play a role in the pathogenesis of some of the complications of diabetes [34]; however, further studies are needed. In contrast, hypermagnesemia in patients with diabetes was more frequent during renal insufficiency and end-stage renal disease [35, 36], and limited studies have reported on the effect of untreated hypermagnesemia on the progression of kidney disease.

Furthermore, hypokalaemia or hyperkalaemia are often observed in patients receiving healthcare [37] and may lead to several renal function abnormalities [38], which may be amplified in patients with diabetes.

# 2. Materials and Methods

## 2.1 Study Setting

The research conducted at the endocrinology and chronic disease (CDC) clinics at Oud Al-Touba Diagnostic and Screening clinic, one of the ambulatory healthcare centres in the emirates of Abu Dhabi in United Arab Emirate. Oud Altouba Clinic is part of the Ambulatory Healthcare Services (AHS) and integrated with Abu Dhabi Healthcare Company (SEHA), the largest healthcare network in UAE.

The AHS clinics provide the most comprehensive health care services with more than 43 speciality services, including Chronic Disease Clinic (CDC), endocrinology, cardiology, family medicine, and nutrition clinics. Besides, a pharmacy providing specialised clinical services, and patient and family health education programs.

## 2.2 Research Design

This is a randomised controlled, multidisciplinary trial. This research is a single-centre study, involving a 12-month follow-up period or till the date of participant withdrawal due to any cause, whichever comes first. The Study is not funded or supported by any grant or institute.

## 2.3 Study Participants

The study will recruit Emirati patients previously diagnosed with T2DM from the endocrinology or chronic disease (CDC) clinics, who have will match the research inclusion criteria and have been taking the same diabetes medications for 12 weeks before the study with regular follow-up schedules in the previous year. Eligible patients will be randomized and blinded to the intervention and control groups.

The patients will be included in the analysis are those whose records are available in Salamtak (electronic medical record system operated by the Salamtak platform). At the end of the study, those with a medical history of cancer, chronic liver disease, high cardiovascular risk (defined as a 10-year predicted atherosclerotic cardiovascular disease (ASCVD) risk of ≥7.5% using the pooled cohort equation or a Framingham Risk Score of ≥20%), cardiac surgery within the last 12 months or any diabetic macrovascular complications will be excluded. Moreover, patients will be excluded either if they withdraw from the study or have a missed follow-up data including missed laboratory tests at the end of study period as per study protocol.

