## 2.6 Randomization

Randomization processes will be performed by a computer-generated random number in Excel Microsoft Office to generate an allocation sequence for each participant in the intervention and control group by the equation (=UNIQUE(RANDARRAY(239,1,1,300,FALSE)), with allocation concealment by sequential numbering representing the participant’s turn in joining the study. All patients identifying data will be removed to conceal randomisation and minimise predictability of the generated random sequence.

Each patient will be assigned a code documented in the consent form and the data entry sheet by the principal investigator, and this information will be saved in a password-protected file. Participants in the intervention group will be identified electronically one week before the next refill schedule or follow-up visit. The control group will continue to receive routine care provided in the clinic during the study period without any interfere in their follow-up appointments.

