Each participant in the intervention group will receive a 15- to 30-min counselling session at the initial visit and each scheduled follow-up visit which will occur every 3 months. During these sessions, the pharmacist will assess medication adherence with a validated adherence questionnaire (Appendix 3) and counsel the patients on the importance of medication adherence on clinical outcomes. The barriers to medication adherence will be identified, discussed with the patient, and resolved as much as possible. Finally, the patient will be provided with two or three months of medication supply, and the medication refill date will be documented for medication adherence calculation using the medication possession ratio (MPR) [42, 43].

After each visit, each participant in the intervention group will receive a 15-minute follow-up phone interview within two weeks for adherence reinforcement and to address any non-compliance issues or medication side effects. Moreover, they will be scheduled for their next medication refill and follow-up visits in the clinic appointment system. Appointments will be scheduled at months 3, 6, and 12 from the initial visit according to the patient’s preferred date, and they will receive a reminder phone call three days before the next visit from the clinic call centre.

Medication adherence will be evaluated using two techniques during the follow-up period: calculating the medication adherence possession ratio and the medication adherence questionnaire scores.

1. Medication Adherence Possession Formulas

In this study, we will use three formulas to calculate medication adherence from patients’ medication refills recorded in Salamtak:

1. Total Fixed Medication Possession Ratio (MPRt)

A fixed medication possession ratio (MPR) formula will be used to measure total (composite) adherence to all medications (MPRt) [44, 45]. The MPRt will be calculated for three chronic regimens including antihyperglycaemic, antihypertensive and antihyperlipidaemic regimens.

For the total MPRt, no regimen-specific MPR (MPRs) will be measured. It is calculated by summing the days’ supply of medication per prescription, then dividing by the number of days of patient follow-up, using a fixed follow-up period of 365 days (12 months) as a constant denominator, adjusted to hospital stay if the participant was admitted during the follow-up period (Figure 2).

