MTM will be effectuated during the counselling session for 15–30 min at the time of dispensing medication. Each patient interview will implement the five criteria for MTM, including medication review to optimise patient treatment as per the latest treatment guidelines, assessment of the possibility of deprescribing, evaluation of any prescribed non-formulary drugs, patient counselling, and provision of printed medication educational materials, particularly for new, high alert, and narrow therapeutic index medications from an evidence-based drug reference to ensure the safe and proper use of these drugs (Lexicomp Online) (Appendix 4).

Moreover, the counselling session will include counselling on potential drug-drug or drug-food interactions and the proper use of any device or over-the-counter (OTC) medication the patient was using. Any detailed disease information or drug modifications required will be discussed and resolved by the treating physician.

Medication reconciliation and chart review will be carried out through the Salamtak local network, integrated with all governmental hospitals, ambulatory clinics, and private institutes in the Emirates of Abu Dhabi in the UAE.

The number and type of pharmacy clinical interventions, in addition to antihyperglycaemic deprescribing, will be analysed and compared between the two groups at the end of the follow-up period.

- 1. Patient Medication Booklet

A pocket-sized patient-specific medication booklet will be provided to each participant in the intervention group (Appendix 5). This initiative in the MPIP aims to promote medication adherence in elderly patients and those with low digital skills. Moreover, the booklet helps to track OTC drugs or herbal medications bought from community pharmacies and enables patients as well as community pharmacists to fill in the name of the drug and the dose by hand, which are then manually added to the patient’s medical record in Salamtak at the next MPIP visit.

During the counselling session, the counselling pharmacist will attach the prescribed medication labels to the booklet and will ensure that the booklet is filled with an updated list of all prescribed medications, medication doses, allergies, next scheduled refill, and any OTC drugs the patient is currently taking (Appendix 5).

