Moreover, both groups will complete a pre-assessment nutrition knowledge questionnaire with eight questions evaluating knowledge of the importance of frequent laboratory blood tests; regularly monitoring of kidney function; recommended dietary allowances of Na, K, and Mg; food sources of these elements; and symptoms of deficiency. Moreover, they will receive educational information based on dietician evaluation as part of routine care in the clinic (Appendices 10 and 11).

Participants in the control group will not receive any advice on carbohydrate calculation, healthy plate model, or specific exercise instructions during the study period. Participants in all groups will be asked to report any modifications in their usual diet or activities throughout the study period.

C) Structured Diet and Dietary Carbohydrate Count Education

The intervention group will receive an educational reinforcement session for a structured diet at each follow-up visit by the same specialised dietitian. Dietitian appointments will be performed concurrently after each follow-up visit to the treating physician appointment to build on physician advice; and included nutrition counselling to reinforce balanced caloric and mineral intake, as well as measuring adherence to structured diet plans.

In the structured diet therapy, the dietitian will set individualised carbohydrate (carb) targets for each participant for eating meals or snacks during the day to cover daily macronutrients, considering the participants’ current eating patterns, food preferences, motivation, and ability to follow the recommended diet.

The total daily calories required by each participant will be calculated according to the United Arab Emirates (UAE) ministry of health and prevention recommendations [53], and based on the basal metabolic rate (BMR) calculations [54] considering the appropriate activity factor based on the participants’ lifestyle and work (Table 2).

Table 2: Calorie-calculation based on BMR and activity factors.

| Lifestyle and exercise frequency | Activity factor |
| --- | --- |
| Sedentary (little or no exercise) | BMR x 1.2 |
| Lightly active (light exercise/sports 1-3 days/week) | BMR x 1.375 |
| Moderately active (moderate exercise/sports 3-5 days/week) | BMR x 1.55 |
| Very active (hard exercise/sports 6-7 days a week) | BMR x 1.725 |
| Extra active (very hard exercise/sports & physical job or 2x training) | BMR x 1.9 |

Basal metabolic rate (BMR) calculations for men and women:

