In each food log section, the participants can describe the consumed food or beverage, and any other oil, fats, sauces, or condiments used in preparation or added during food serving, in addition to the time and occasion of each meal or snack. During the session, the research dietitian will review the food logs, clarify any unclear entries or descriptions, and estimates the average daily energy intake and dietary carbohydrate value for each participant.

D) Exercise and Physical Activity Reinforcement Counseling

For each participant in the intervention group, the dietitian will develop individual exercise targets based on their clinical condition and motivation level while taking into consideration each participant’s current eating patterns and willingness to adhere to exercise and lifestyle modifications.

Any identified challenges that limit the patient from being physically active will be discussed with the patient, and an action plan will be discussed with the treating physician and documented in the patient’s file.

Anthropometric measurements will be obtained by registered nurses in the clinic at the time of enrolment, before exiting the study for all participants, and at each follow-up visit for the intervention group. Body weight and height will be measured without shoes using a standard monthly calibrated scale at the Dietitian Office (Tanita Corporation, Japan). The same nurse will measure the patients’ waist circumference just marginally above the hipbone and their hip circumference at the largest part of their buttocks.

In addition, to explore the type of most recurring physical activity in our intervention population, we added additional table to the questionnaire to describe the type of physical activity, intensity of the purposive activity, average number of days per week for each activity, and duration of each activity (Appendix 14).

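### Section 2.3 claims a blinding that the design cannot have, and the self-reported parts of primary outcomes 1 and 2 are open to differential reporting

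*Protocol*

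**What the plan says.** **Blinding.** Protocol section 2.3 says "Eligible patients will be randomized and blinded to the intervention and control groups". Blinding is mentioned nowhere else.

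**What each arm receives.** Section 2.6 says "The control group will continue to receive routine care provided in the clinic during the study period". Section 2.8.2 B adds "Participants in the control group will not receive any advice on carbohydrate calculation, healthy plate model, or specific exercise instructions during the study period". The intervention arm receives counselling sessions and follow-up calls, a booklet ("A pocket-sized patient-specific medication booklet will be provided to each participant in the intervention group") and app training under section 2.8.1. Under section 2.8.2 it receives individual carbohydrate targets and a monthly coaching call.

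**Who measures.** The first primary outcome in section 1.3 is "to evaluate the impact of pharmacist-led MTM on medications adherence". Section 2.8.1 measures adherence by refill-based MPR and by a four-item yes/no questionnaire, and ranks neither above the other. In the intervention sessions "the pharmacist will assess medication adherence with a validated adherence questionnaire (Appendix 3) and counsel the patients". The second primary outcome covers anthropometry and carbohydrate and energy intake. The intervention arm gets an "educational reinforcement session for a structured diet at each follow-up visit by the same specialised dietitian", and in session "the research dietitian will review the food logs, clarify any unclear entries or descriptions, and estimates the average daily energy intake". Section 2.8 names a clinical pharmacist and a specialised dietitian as assessors in both arms at entry and exit. No masked or independent assessor is named.

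**The concern.** The first problem is one of fact. A patient who is handed a booklet, taught to count carbohydrate and telephoned every month knows which arm they are in, and so do the pharmacist and dietitian. If the blinding claim is carried into the trial report, readers will trust the results more than the design allows.

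The second problem follows from the first. Answers to four yes/no adherence questions and entries in a 3-day food log depend on recall and on the wish to please. In the intervention arm they are given to the people who do the coaching. That arm also answers the questionnaire and completes the log at follow-up visits, while controls do so only at entry and exit. Intervention patients could therefore report better adherence and lower intake without any change in behaviour. Because section 2.8.1 sets the questionnaire beside MPR without ranking them, a positive questionnaire alone could be reported as improved adherence.

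**Working it through.** **Step 1. Could the blinding claim be true in some other sense?** It might have meant allocation concealment. But section 2.6 deals with concealment separately, and section 2.3 speaks of patients being blinded to the groups. Section 2.6 also has intervention participants identified electronically a week before each refill or visit, so staff know the arm too. The claim contradicts sections 2.6, 2.8.1 and 2.8.2.

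**Step 2. Which primary measures depend on self-report?**

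| Primary outcome (section 1.3) | Measure | Source | Self-reported to a deliverer? |
|---|---|---|---|
| 1 Adherence | MPR (used for sizing) | refill records, 2.8.1 | no |
| 1 Adherence | four-item questionnaire | pharmacist, 2.8.1 | yes |
| 2 Diet and anthropometry | BMI (used for sizing), weight, waist, hip | nurses, 2.8.2 D | no |
| 2 Diet and anthropometry | carbohydrate, energy intake | food log and dietitian, 2.8.2 C | yes |
| 3 Diabetic outcomes | HbA1c (used for sizing), lipids | laboratory | no |
| 3 Diabetic outcomes | blood pressure | clinic measurement | no |

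**Step 3. The plan's own sample size.** For MPR, section 2.10 gives difference 0.035, SD 0.09, power 80%, alpha 5%, and 82 per group.

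n per arm = 2(z_alpha + z_beta)² (SD/difference)², with SD/difference = 0.09/0.035 = 2.571.

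- One-sided: 2 × (1.645 + 0.842)² × 2.571² ≈ 82, which reproduces the stated figure.
- Two-sided: 2 × (1.960 + 0.842)² × 2.571² ≈ 104.

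The protocol does not state the number of sides. That is a separate point, but it affects how Step 4 is read.

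**Step 4. Illustration: no true effect, reporting shift of b SD, 82 per arm.** The standard error of the mean difference in SD units is √(2/82) = 0.156. The chance of two-sided p<0.05 is Φ(b/0.156 − 1.96) + Φ(−b/0.156 − 1.96).

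| b (assumed) | b/0.156 | two-sided p<0.05 | one-sided 5% |
|---|---|---|---|
| 0 | 0 | 5.0% | 5.0% |
| 0.1 | 0.64 | 9.8% | 15.8% |
| 0.2 | 1.28 | 24.9% | 35.8% |
| 0.3 | 1.92 | 48.4% | 60.9% |
| 0.4 | 2.56 | 72.6% | 82.0% |

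An observed difference of 1.96 × 0.156 = 0.31 SD is just significant. With 90 per arm, shifts of 0.2, 0.3 and 0.4 SD give 26.9%, 52.1% and 76.5%. More patients do not help, because the bias stays while the standard error shrinks.

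**Step 5. The same calculation in grams of carbohydrate per day.** The protocol gives no SD for intake, so a range is assumed (82 per arm, two-sided).

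| Assumed SD | shift 10 g | shift 15 g | shift 30 g |
|---|---|---|---|
| 40 g | 36% | 67% | 99.8% |
| 60 g | 19% | 36% | 89% |
| 80 g | 13% | 23% | 67% |
| 100 g | 10% | 16% | 48% |

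The result depends heavily on the assumed SD and shift. The calculation uses a normal test. Section 2.10 plans a Mann–Whitney test for non-normal data, so for a 0–4 score these figures are approximate.

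**The case against.** **Reach.** A reader might infer that all the primary outcomes are compromised, or that expectation bias could explain a positive trial. The protocol does not support that. The measures that size the three outcomes in section 2.10 are refill-based MPR, BMI and HbA1c, and none of them is a patient's report to a coach. This part of the objection stands in full. MPR carries a different caveat: section 2.8.1 has the programme supply two or three months of medication and schedule the next refill, so MPR may move through refill handling. That is not reporting bias.

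**Scoring.** One might also infer that the pharmacist's judgement colours the questionnaire score. It does not, because four yes/no items are summed by a fixed rule (Table 1). Only the eliciting of answers is exposed. For the food logs, both clarification and estimation involve judgement.

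**Same assessors.** Section 2.8 uses the same professional roles in both arms at entry and exit. That is correct, but prior contact still differs between arms. The protocol assigns these tasks by role, and nothing in it separates assessor from deliverer.

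**Size.** Every bias size and SD above is assumed. The arithmetic would fit any unmasked two-arm trial of this size and does not show that such bias is likely here. This stands.

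**Inherent limitation.** Counselling trials are usually open-label, and this one is unfunded and single-centre. An SAP, not seen here, might rank the adherence measures. Both points lower the severity, but neither makes the statement in section 2.3 true.

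**Conclusion.** The point holds in a limited form and should be fixed. Section 2.3 attributes to the trial a blinding that sections 2.6, 2.8.1 and 2.8.2 rule out for patients and for the staff who deliver the intervention. The trial is open-label.

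Differential reporting could produce a positive result on two self-reported components: the questionnaire score within outcome 1, and food-log carbohydrate and energy intake within outcome 2. The 25%, 48% and 73% at shifts of 0.2, 0.3 and 0.4 SD assume 82 per arm, no true effect, a two-sided 5% test and approximate normality. They show how sensitive the comparison is and do not estimate the bias in this trial, which cannot be sized from the protocol. The conclusion does not extend to MPR, anthropometry, HbA1c or lipids.

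**What to change.** 1. In section 2.3, remove the claim of blinding and state that the trial is open-label for patients and staff.
2. State that the measures used for sizing in section 2.10 decide outcomes 1 to 3: refill-based MPR, measured BMI and laboratory HbA1c. Describe questionnaire score and self-reported intake as supportive and unmasked.
3. Have patients complete the four-item questionnaire themselves, before any pharmacist contact, at both baseline and exit and in both arms. Changing the exit visit alone would make the mode of administration differ between the two time points.
4. Where existing staff allow, take the analysed intake values from baseline and exit logs coded without arm or visit. State the limits: a dietitian who has already reviewed a log in session may recognise it, and coding does nothing about patients' own reporting.

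**Cost.** Items 1 and 2 are changes of wording. Item 3 changes the order of events at two visits. Item 4 adds some log handling and a second estimate for analysis. The price is a weaker claim for the self-reported measures. The sample size does not change on this account.
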